**Step 4: End line data collection, analysis and report writing**

Step 2: Religious leaders’ training by project PI

Training contents: Maternal health message contents, flip chart, poster and group education

Trained religious leaders led SBCC to improve maternal health behavior

Figure 3. Presents the intervention processes and package of trained religious leaders led SBCC.

| Session | **Content of the message** | **Dose** | **Strategy of delivery** | **Frequency** | **Compliance parameters** | **Responsible person** |
| --- | --- | --- | --- | --- | --- | --- |
| Session 1 | - Major causes of maternal and new-born Illness and death | 1:00 hour | • Brain storming • Group education/ Group work • Case study/ case scenario • Question and Answer (Q&A) • Agree/ Disagree exercises • Group Presentation | Once at their 2^nd^ trimester period | -% pregnant mothers participated | Researcher and trained religious leaders |
| Session 2 | - Focused Antenatal Care - About danger signs during pregnancy | 1:00 hours | Brain storming • Group education/ Group work • Case study/ case scenario • Question and Answer (Q&A) • Agree/ Disagree exercises • Group Presentation | Once at their 2nd trimester period | -% pregnant mothers participated | Researcher and trained religious leaders |
| Session 3 | - Birth preparedness and complication readiness - Danger signs, labor and childbirth, - Components of postnatal care and Postnatal danger signs and neonatal danger signs | 1:00 hour | Brain storming • Group education / Group work • Case study/ case scenario • Question and Answer (Q&A) • Agree/ Disagree exercises • Group Presentation | Once at their 3^rd^ trimester period | -% pregnant mothers participated | Researcher and trained religious leaders |
| Session 4 |  | 1:00 hour | Brain storming • Group education / Group work • Case study/ case scenario • Question and Answer (Q&A) • Agree/ Disagree exercises • Group Presentation | Once at their 3^rd^ trimester period | -% pregnant mothers participated | Researcher and trained religious leaders |
|  | **Providing specific take-home print materials**   - ANC practices - SDS practice | -Poster  -Information card  -Flip chart | - | Delivered during in each training session | -% of pregnant mothers received print materials | Researcher and trained religious leaders |
|  | **End line data collection** | - | - | at 4^th^ month of intervention | % pregnant mother interviewed | Researcher, supervisors data collectors. |

Table 2 protocol interevention

**The focuses of training (intervention key messages) on:**

**Antenatal care:** (taking TT injection, taking Calcium Consumed 100+ IFA tablets , eating more food during pregnancy, eating Green vegetables , eating Fruits during pregnancy , drinking milk during pregnancy , eating pulses and beans during pregnancy , taking nap/rest, regularly during pregnancy, Husband accompanying for ANC (regularly /mostly), Human immunodeficiency virus (**HIV)**  **and syphilis** test, tobacco use and substance use. **Benefits of early and exclusive breastfeeding (**Provides the best nutrition for the new-born Is easily digested and efficiently used by the baby’s body, Protects against infection and other illnesses, Offers some protection against allergies, Is cost-effective and affordable, Promotes mother-baby bonding. **Unhealthy beliefs and practices about feeding new-borns**, **Hygiene during pregnancy**, **Breastfeeding and contraception, Benefits of birth spacing: (**Maternal mortality, fetal death (miscarriage or stillbirth), neonatal mortality, Anaemia in the mother during subsequent pregnancies, Postpartum inflammation of the endometrium lining the uterus, Premature rupture of the amniotic membranes surrounding the fetus, Premature birth, Intrauterine growth retardation and a low birth-weight baby and Malnutrition of new-borns and infants due to insufficient breast-milk**).**

**Prenatal Danger signs: (**Severe headache, Blurred vision, Fatal movement absent, High blood pressure, Edema of the face/swelling, Oedema of the hands/leg swelling, Convulsions, Excessive vaginal bleeding, Severe lower abdominal pain and Leaking fluid (meconium stained).

**Labor/delivery** **Danger signs: (**Excessive vaginal bleeding, Foul-smelling discharge, High fever, Baby’s hand or feet coming out first, Baby is in abnormal position, Prolong labor (.12 hours), Retained placenta, Rupture uterus, Cord prolapse, Cord around neck and Convulsion).

**Postpartum Danger signs:** (Excessive vaginal bleeding**,** Foul-smelling discharge**,** High fever**,** Inverted nipples**,** Tetanus**,** Retained placenta**,** severe abdominal pain**,** Convulsions **and** Engorged breasts/swelling of breasts)

**Neonatal Danger signs: (**Poor feeding or unable to suck**,** Diarrheal**,** Redness around the cord**,** Red eye/discharging eyes**,** Difficult breathing**,** Yellow coloration of the skin/jaundice**,** Hypothermia/shivering**,** Blisters on skin/Skin lesion**,** Baby doesn’t cry**,** Fever**,** Unconscious**,** Fast breathing**,** Chest in drawing**,** Doesn’t pass urine**,** Doesn’t pass stool and Convulsions.

**Consulting doctor or others health professionals:** if they have danger signs (during pregnancy, labor and childbirth, 42 days after delivery, and neonatal danger signs).

**Birth preparedness and complication readiness:** (plan for where to give birth, plan for a skilled birth attendant, plan to save money, plan for transportation and identification of compatible blood donors in case of emergency).

**Delivery at a health facility with a skilled provider** and **postnatal care:** (Women discuss FP method with husband Women adopted FP method after delivery Mother fed colostrum to the baby).

**Group training of pregnant mothers by Religious leaders**

Each trained religious leader will be assigned to deliver group training for pregnant mothers residing in cluster. The trained religious leaders will deliver a total of four group training sessions for the pregnant mothers they are assigned with the same training procedures provided by the researcher during training of religious leaders. Religious leaders will be trained to conduct culturally appropriate training sessions with pregnant mothers using facilitator manual and posters prepared in the local language.

**Control group (standard care)**

The control group in this study will be on the existing routine maternal service without a provision of religious leaders’ training intervention. In this arm, there will be no intervention by the researchers, rather baseline and end line data will be collected.

## 4.14 Cluster and individual selection

Health posts are eligible for trial. All 40 health post units in the selected districts are eligible and 12 health posts are randomly selected for the trial using a computer random number generator. Pregnant mothers less than or equal to 20 gestational age are eligible to participate in the trial if they are living in the villages within the selected health post village areas. Baseline surveys will be commenced in May 2022 and end line surveys are scheduled to begin after four months of intervention.

The pregnancy surveillance for this study will be conducted among currently married women of reproductive age (15–49 years) permanently living in the selected districts. A pregnancy test will be done for the study women at the beginning of the surveillance. Identifying pregnant women will be a two-step process. First, all women will be screened using pregnancy screening questions adapted from the Kenya family planning enrolment questionnaire as published in the Lancet (Stanback J et al, 199) (Table 2). If the answer to at least one of the six pregnancy screening questions is ‘yes’, pregnancy will be ruled out. Women who respond in a way that suggested the possibility of being pregnant is asked to provide a urine sample for a pregnancy test, which will be done using a dipstick in the respondent’s home. Once pregnancy is detected, the women will be recruited for the trial study.

Table 2 Pregnancy screening questions adapted from Kenya family planning screening questions

| S/No | Items | Yes or No |
| --- | --- | --- |
| 1 | Have you given birth in the past 4 weeks? |  |
| 2 | Are you less than 6 months post-partum or fully breastfeeding and free from menstrual bleeding since you had your child? |  |
| 3 | Did your last menstrual period start with in the past 7 days? |  |
| 4 | 4 Have you had a miscarriage or an abortion in the past 7 days? |  |
| 5 | Have you abstained from sexual intercourse since your last menses? |  |
| 6 | Have you been using a reliable contraceptive (pills, injectable, and Norplant) method consistently and correctly? |  |

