# Chapter four Methods and Materials

## 4.1 Study settings and period

This study will be conducted in the two rural districts (Lemo and Amaka) of Hadiya Zone in Southern Ethiopia. Hadiya zone is divided into 13 rural Districts and two administrative towns with total of 329 kebeles from which 303 of them rural and 26 of them were urban. Each district is divided into kebeles**;** the lowest administrative units in Ethiopia. Hadiya Zone hosts a total of 1,573,841 populations with a total area of 3542.66 Km^2^. Hadiya zone has an estimated 54455 pregnant mothers. Population of the Lemo District is 148,339. From this 73,390 are males and 74,950 are females. There are 34,563 women in reproductive age group from which 5133 is expected pregnancy. Total population of Amaka district is 80857, 4125 are females and 39622 is males. Expected pregnancy is 2797. Protestant, orthodox and Muslim are the three dominant religions in Hadiya zone. 75.35% of the population are [Protestants](https://en.wikipedia.org/wiki/P%27ent%27ay), 11.13% are [Muslim](https://en.wikipedia.org/wiki/Islam_in_Ethiopia), 8.45% are Ethiopian Orthodox Christians, and 4.31% are [Catholic](https://en.wikipedia.org/wiki/Roman_Catholicism_in_Ethiopia). This study will be conducted between October, 2022 annd May, 2023.

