## 4.5 Inclusion and Exclusion Criteria

**Inclusion criteria**

- Pregnant women less than 20 weeks gestational age
- Living in selected kebele
- Pregnant women willing to participate in the study

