## 4.8 Sample size

In accordance with the main objective of the larger study, the sample size estimate is designed to detect changes in the proportion of skilled delivery service utilization. The sample size is calculated using stata software based on the following assumptions. Tail (s): One; effect size (d): 0.15; **α** error probability = 0.05; power (1-**β** error probability) = 0.8, and allocation ratio (N1/N2) = 1. This gives a sample size of 155. Then, adding design effect, DE = 1+(m-1)ICC , where m=Average cluster size, m= 50, ICC=0.02 based on a published study ICC (Killip et al., 2004), DE=2, and allowing for a 10% loss to follow up, the total sample size is 682 (N1 = 341 and N2 = 341). N1 and N2 are sample sizes in the control and intervention group, respectively. Based on these assumptions, the estimated sample size is: 306 pregnant mothers per group to detect a 15-percentage point anticipated difference in the proportion of skilled delivery service utilization (an increase from 26% to 41%). This estimate is based on the baseline skilled delivery service utilization in the Ethiopia Demographic and Health Survey (26% from EDHS 2016, SNNP region report) in the control group (CSA, 2016).

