## 4.17 Data collection and management

The principal investigator will train the data collectors and supervisors for two
consecutive days on instruction; in the quantitative method, study guides, role-plays
(demonstration), informed consent, how to approach participants, how to collect data using
mobile health, ethical procedure and general information and the objective of
the study. The data will be collected by using a mobile-based application called open data kit
(ODK). In the initial step, a pre-intervention survey will be conducted after the randomization and allocation. And there will be two times data collection including the pre-intervention and post-intervention data. The data will be collected by 4 months interval to have a good longitudinal data. The type of data will be panel data with repeated cross-sectional. Experienced data collectors with health background and Hadiyisa speaking will be recruited to collect the data. Besides, a master holder with health profession will be employed to supervise the whole data collection process.

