**End line Data collection**

The same procedure with the baseline data will be repeated to collect the end line data after one month of delivery. Six data collectors with health background will be used to collect the data. Two supervisors will be assigned to check for the daily activity, consistency, and completeness of the questionnaire and to give appropriate support during the data collection process. The data collectors and the supervisors will be assigned to a different cluster of a given district.

Qualitative Data collection

Focus group discussions and in-depth interviews among religious leaders and pregnant mothers will be conducted. Trained graduate research assistants will conduct Focus group discussions and in-depth interviews. Data will be collected by recording interviews by audiotape. Brief field notes will be taken during interviews. Field notes will be carefully taken during data collection and analysis. These notes will collect observations and assumptions about what will be heard or observed and personal narratives about what will be felt by the researcher during an interview.

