**Operational definition**

**Skilled delivery service utilization**

Skilled delivery service utilization will be measured based on women who gave birth in health center and hospital by assistance of health professionals that have midwifery skills including Midwife nurse, Nurse, Health Officers and Doctors *as* reported by the participant.

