**Part VI Perception of Pregnancy Risk**

1. The risk for myself during this pregnancy is:

No Risk Extremely

At All High Risk

2. The risk for my unborn baby during this pregnancy is:

No Risk Extremely

At All High Risk

3. My risk of haemorrhaging (losing too much blood) during this pregnancy is:

No Risk Extremely

At All High Risk

4. My risk of having a caesarean section is:

No Risk Extremely

At All High Risk

5. My risk of dying during this pregnancy is:

No Risk Extremely

At All High Risk

6. My baby’s risk of being born prematurely is:

No Risk Extremely

At All High Risk

7. My baby’s risk of having a birth defect is:

No Risk Extremely

At All High Risk

8. My baby’s risk of needing to go to the Neonatal Intensive Care Unit is:

No Risk Extremely

At All High Risk

9. My baby’s risk of dying during this pregnancy is:

No Risk Extremely

At All High Risk

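### The protocol gives incompatible endline times; at a four-month interval with a prompt start few women would have delivered, so skilled delivery would be largely unobserved

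*Protocol*

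**What the plan says.** Two kinds of endline timing stand in the protocol.

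- **About four months.** Section 4.14: "end line surveys are scheduled to begin after four months of intervention". Section 4.17, Data collection and management: "The data will be collected by 4 months interval to have a good longitudinal data". The intervention table in 4.13 puts endline data collection in the fourth month of the intervention. The Summary and 4.11 also speak of four months, but can be read as counting from the start or from the end of the intervention.
- **Tied to delivery.** Section 4.17, End line Data collection: "The same procedure with the baseline data will be repeated to collect the end line data after one month of delivery".

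Eligibility in 4.5 is "Pregnant women less than 20 weeks gestational age"; 4.14 admits women at exactly 20 weeks as well. Section 4.8 says that "the sample size estimate is designed to detect changes in the proportion of skilled delivery service utilization". The operational definition in 4.18 reads "Skilled delivery service utilization will be measured based on women who gave birth in health center and hospital", so the outcome exists only once the woman has given birth. On dates, 4.1 says "This study will be conducted between October, 2022 annd May, 2023", while 4.14 and the participant timeline start baseline in May and June 2022.

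**The concern.** The two timings produce different data. A survey four months after baseline would meet most women while still pregnant, if the intervention starts promptly. They would have no value for skilled delivery in the index pregnancy, and objective 3 would be close to unanswerable. The few deliveries seen would be preterm or early-term births in women enrolled near the gestational limit, who are not representative of the sample.

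The questionnaire could hide the gap. Annex 1 serves both surveys, and its item on the place of a specific delivery, question 324, asks about the last child. A woman still pregnant would answer for an earlier birth, which the intervention cannot have affected. The data would look complete but would not measure the trial outcome. The indicator for four or more antenatal visits would be counted partway through pregnancy.

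The delivery-based timing has its own mismatch. The pregnancy-risk items in Annex 1 Part VI, such as "My risk of dying during this pregnancy is", do not fit a woman who has already given birth.

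**Working it through.** The protocol gives no figure for gestation at endline or for the share delivered, so there is none to reproduce. The check needs only the entry limit (4.5), the four-month interval (4.14, 4.17) and stated assumptions about entry and delivery.

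**Gestation at a four-month endline, with no lag before the intervention**

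4 × 30.44 / 7 = 17.4 weeks.

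- Entry at 20 weeks: 20 + 17.4 = 37.4 weeks
- Entry at 12 weeks: 12 + 17.4 = 29.4 weeks
- Entry at 8 weeks: 8 + 17.4 = 25.4 weeks

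**Share delivered by then**

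Share = P(gestation at delivery ≤ gestation at entry + lag + 17.4 weeks). Assumptions: entry uniform from 4, 6, 8 or 13 weeks up to 20; delivery normal with mean 39 or 40 weeks and SD 2. The low end of each range is entry from 4 weeks with mean 40. The high end is entry from 13 weeks with mean 39.

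| Lag from enrolment to intervention | Delivered | At least one month postpartum |
| --- | --- | --- |
| None | 0.6% to 3.4% | about 0% |
| 15 days (length of the baseline survey, 4.17) | 3.7% to 15.6% | at most 0.3% |
| 58 days (assumed) | 35% to 86% | 10% to 35% |

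The 58 days come from reading the date columns of the work plan in order. Which activity belongs to which date cannot be recovered from the text, so this row is only a sensitivity case.

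With 341 women recruited per arm (4.8 and the figure in 4.11), the first row means about 2 to 12 women per arm with an observed delivery (341 × 0.006; 341 × 0.034). The second means about 13 to 53 (341 × 0.037; 341 × 0.156).

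**Time from enrolment to one month after delivery, assuming delivery at 40 weeks**

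(40 − gestation at entry) + 4.35 weeks.

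- Entry at 20 weeks: 24.35 weeks, or 5.6 months
- Entry at 4 weeks: 40.35 weeks, or 9.3 months

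Both exceed four months, so a four-month interval cannot satisfy the delivery-based timing for any woman who delivers at 40 weeks.

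**Study period in 4.1**

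1 October 2022 to 31 May 2023 is 242 days, or 34.6 weeks. A woman enrolled on the first day completes follow-up inside it if (40 − entry) + 4.35 ≤ 34.6, that is, entry at about 9.8 weeks or later. Enrolment 14 days later moves the limit to about 11.8 weeks.

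**The case against.** A reader might infer that endline is fixed at four months after enrolment, so that the primary outcome cannot exist when it is measured. The protocol does not support that.

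- Endline is not fixed. The paragraph written specifically for endline collection ties it to delivery, when the outcome can be observed.
- Section 4.14 counts from the intervention, not from enrolment. The Summary and 4.11 could mean four months after a four-month intervention ends. That is about eight months from its start (34.8 weeks), when most women would have delivered. Only the interval in 4.17 clearly runs from survey to survey.
- The lag before the intervention is not stated. The 4.13 table places the first two sessions in the second trimester and the last two in the third. A woman enrolled at 4 weeks would be at only 21.4 weeks after four months, so a prompt start does not fit that table for the earliest entrants. A share delivered of practically zero is therefore not a safe figure.
- The protocol never calls skilled delivery the primary outcome. Section 4.7.1 lists it beside antenatal care; 4.8 sizes the trial on it.
- The period in 4.1 is not too short for everyone, and other sections give earlier baseline dates.
- The arithmetic follows the same women over time, whereas 4.11 describes repeat cross-sectional surveys and 4.17 a mixture of panel and repeated cross-section.

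All of this stands, and it limits the size of the problem. It does not remove the conflict: the interval in 4.17 and the delivery-based paragraph under the same heading give different endlines. Even with the assumed 58-day lag, at most 35% of women would be one month postpartum. The several possible starting points for the four months are a further reason to reconcile the text.

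**Conclusion.** The contradiction is real and should be resolved before fieldwork. The 4.13 table, 4.14 and the interval in 4.17, and on one reading the Summary and 4.11, put endline about four months after baseline or intervention start; the End line Data collection paragraph puts it one month after delivery. If the four-month text is followed with a prompt start, roughly 1% to 3% of women would have delivered, or 4% to 16% with a 15-day lag. Skilled delivery would then be largely unobserved and the antenatal count truncated. These percentages rest on the assumed distributions and on the lag, and rise if the lag is longer. The 37.4-week ceiling needs only entry by 20 weeks, a four-month interval and no lag. The period in 4.1 is too short only for women enrolled before about 10 weeks, or about 12 weeks if enrolment takes place two weeks in.

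**What to change.** State one endline for the women enrolled at baseline: an interview about one month after each woman's own delivery, as the End line Data collection paragraph already has it. Align the Summary, 4.11, the intervention table in 4.13, 4.14 and the interval sentence in 4.17 with it. Say explicitly that the enrolled women are followed, since 4.11 and 4.17 describe the surveys differently.

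At endline, word question 324 to refer to the birth that ended the index pregnancy. Reword or omit the pregnancy-risk items that speak of the current pregnancy. Reconcile the dates in 4.1, 4.14, the participant timeline and the work plan, so that follow-up covers about 5.6 to 9.3 months after enrolment (assuming entry at 4 to 20 weeks and delivery at 40).

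No extra women or interviews are needed. The cost is a longer, staggered field period: individually timed visits replace a block survey by six data collectors, and the 256,000 Birr budget should be checked against that.

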## 4.15 Intervention assignment and masking

Randomisation is stratified by kebeles, with 12 clusters in the district allocated to either control or intervention in a public randomisation meeting. From each clusters (kebele), local stakeholders (HEWs, kebele leaders and religious organization leaders) are invited, a number is allocated to each cluster, the numbers are written on small plastic balls, and placed the balls in a dark bag. Each participant is asked to draw one ball from the bag and read out the cluster numbers out until all balls are picked. The cluster numbers are written on a sheet of paper in order of selection. Participants then place 12 pieces of paper numbered 1 to 12—each corresponding to a unique allocation sequence generated by an independent statistician—in the dark bag, and asked a participant to select a paper and read out the number. The corresponding sequence is then used to publicly allocate each cluster to one of two groups. Because of the nature of the intervention being tested, the intervention team could not be masked to allocation. The data collection team will be masked to allocation, both at the cluster and at the individual level. Blinding is done to control for bias as follows. The researcher does not inform the study interventions and hypothesis for the participants who participate during the randomization of the kebeles into study groups.

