The first training session will be conducted at the beginning of the intervention whereas the second session of similar content will be repeated after one month of the first intervention session and the third and fourth training sessions will be after one months of the second intervention session. After training sessions, every participant will receive a copy of the visual materials (posters) containing the key messages for promoting prenatal health behaviours. Direct, interactive and participatory learner and activity oriented instructional strategies will be delivered. Talks, group discussions, group work exercises, demonstrations, role plays, storytelling, simulation, case studies and problem-solving will be used to enhance knowledge, attitude, and behaviours on maternal and neonatal health (Table 2 shows over protocol of intervention).

Overall project coordination: by PI and co-PIs

Step 1:

Formative assessment: perception of mothers’ on engagement of religious leaders in promoting maternal health, and role of religious leaders in promoting maternal and child health: a qualitative exploration of religious leaders’ perspective

Baseline study: Intervention protocol development, data collection and analysis

Developing strategies and SBCC material flip chart, information card and poster and recruiting religious leaders

Randomization of the clusters in to intervention and control groups

Step 3: Pregnant mothers’ training by trained religious leaders

Training contents: Maternal health message contents, flip chart, poster, group education and group discussion

**Session 1:** Major causes of maternal and new-born Illness and death

**Session 2:** Focused Antenatal Care and danger signs during pregnancy

**Session 3:** BPCR and danger signs during labor and childbirth

**Session 4:** Components of PNC and Postnatal danger signs and neonatal danger signs

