**Baseline Data Collection**

Six clinical nurses for data collection and two supervisors with master holder in public health will be used. Intensive training will be given for data collectors and supervisors on the item. The data collectors and the supervisors will be assigned to a different cluster of a given district. Interviews are expected to last approximately 1 h and will be conducted in a quiet, private space at the homes of the women. If selected women are absent from their homes, interviewers will visit households up to three different days/times to attempt to interview them before the woman will be replaced with another randomly selected woman. The data will be collected for a total of 15 days.

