**Part IX Religious leaders’ engagement scale measurement tool (end-line)**

| 801 | My religious leader was consistent reminder so that I keep ANC follow up based on schedule or appointment | 1. Strongly disagree; 2. Disagree; 3.Neutral; 4. Agree; 5. Strongly agree |  |
| --- | --- | --- | --- |
| 802 | My religious leaders frequently reminded to complete taking iron-folate without interruption | 1. Strongly disagree; 2. Disagree; 3.Neutral; 4. Agree; 5. Strongly agree |  |
| 803 | My religious leaders repeatedly notified us about tetanus toxoid vaccination | 1. Strongly disagree; 2. Disagree; 3.Neutral; 4. Agree; 5. Strongly agree |  |
| 804 | My religious leaders repeatedly notified us about STI and HIV screening and counselling | 1. Strongly disagree; 2. Disagree; 3.Neutral; 4. Agree; 5. Strongly agree |  |
| 805 | My religious leaders commonly prompted us in identifying skilled provider | 1. Strongly disagree; 2. Disagree; 3.Neutral; 4. Agree; 5. Strongly agree |  |
| 806 | My religious leaders commonly encouraged us to give birth at health facility | 1. Strongly disagree; 2. Disagree; 3.Neutral; 4. Agree; 5. Strongly agree |  |
| 807 | My religious leaders commonly encouraged us to prepare transportation during labor | 1. Strongly disagree; 2. Disagree; 3.Neutral; 4. Agree; 5. Strongly agree |  |
| 808 | My religious leaders commonly encouraged us to identify sources of support for me and my family during the birth and the immediate postnatal period | 1. Strongly disagree; 2. Disagree; 3.Neutral; 4. Agree; 5. Strongly agree |  |
| 809 | My religious leaders commonly encouraged us to prepare any additional costs associated with the birth, preparing supplies for my care and the care of my new-born baby. | 1. Strongly disagree; 2. Disagree; 3.Neutral; 4. Agree; 5. Strongly agree |  |
| 810 | My religious leaders repeatedly notified us about danger signs during pregnancy | 1. Strongly disagree; 2. Disagree; 3.Neutral; 4. Agree; 5. Strongly agree |  |
| 811 | My religious leaders repeatedly notified us about danger signs during labour and child birth | 1. Strongly disagree; 2. Disagree; 3.Neutral; 4. Agree; 5. Strongly agree |  |
| 812 | My religious leaders repeatedly notified us about danger signs during post-partum period | 1. Strongly disagree; 2. Disagree; 3.Neutral; 4. Agree; 5. Strongly agree |  |

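### Section 4.15 claims masked interviewers without qualification, but the masking cannot be maintained at end line, when they ask about religious leaders' teaching kebele by kebele

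*Protocol*

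**What the plan says.** Protocol 4.15 makes the masking claim in one sentence: "The data collection team will be masked to allocation, both at the cluster and at the individual level". Just before it, the same section concedes that "the intervention team could not be masked to allocation". The only blinding procedure it describes is that those attending the randomisation meeting are not told the interventions or the hypothesis.

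Other sections bear on whether the claim can hold:

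- **4.16 and Annex 1.** Trained interviewers conduct face-to-face interviews. The questionnaire includes "Part IX Religious leaders’ engagement scale measurement tool (end-line"), items 801 to 835.
- **4.17.** Collectors are trained on the objective of the study and assigned by cluster. Baseline interviews "will be conducted in a quiet, private space at the homes of the women", and the end line repeats the baseline procedure one month after delivery.
- **4.13.** After the training sessions, "every participant will receive a copy of the visual materials (posters"). The intervention table (Table 2 in that section) also lists take-home print materials.
- **4.13, Table 2, responsible persons.** The researcher and the trained religious leaders are named for every session. The end-line row names "Researcher, supervisors data collectors".
- **4.16 and the operational definitions.** Skilled delivery and antenatal care use are as the participant reports them. Knowledge is a count of danger signs named spontaneously.

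**The concern.** An unqualified statement of masking at both levels tells the reader that knowledge of the arm cannot have influenced how outcomes were recorded. The end-line procedures do not deliver that.

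This matters because the outcomes are open to influence. Place of birth and number of visits are taken from the woman's answer, and no check against facility records is described. Knowledge depends on what the interviewer accepts as a spontaneous answer, and in Annex 1, Part V, two of the danger-sign questions instruct the interviewer to probe for more. An interviewer who knows or suspects the arm can probe harder or code more generously. The likely direction favours the intervention, and a reader relying on 4.15 would discount it. The protocol's own literature review (2.8) cites social desirability bias in self-reported data from earlier work with religious leaders.

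**Working it through.** The masking claim has no figure to reproduce, so the first step is to set the sections side by side.

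**Step 1: what the interviewer learns.** Part IX has 835 − 801 + 1 = 35 items on what the woman's religious leaders reminded, taught and followed up; item 806 concerns encouragement to give birth at a facility. The questionnaire title names trained religious leaders' engagement and a cluster randomised trial, and the first field is the kebele name. With training on the objective, the interviewer knows what strong agreement in Part IX would suggest.

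**Step 2: how it spreads.** All women in a kebele share one allocation, so whatever one interview suggests about the arm applies to the whole kebele. Average enrolment is 682 / 12 = 56.8 women per kebele. With one collector per kebele, 1 − 1/56.8 = 98% of interviews follow an earlier Part IX by the same person in that kebele. With all six collectors sharing a kebele it is 1 − 6/56.8 = 89%. These percentages describe interview order only; they do not measure how many interviewers know the arm.

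**Step 3: other cues.** Posters go only to women who attended sessions, and interviews are in the home. A poster may be seen, though the protocol does not say that posters are displayed.

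**Step 4: illustrative size.** The documents give no rate of misrecording. Assume a true 26% skilled delivery in both arms (the control rate in 4.8), a share *r* of intervention-arm home births recorded as skilled deliveries, and none in control. The spurious difference is *r* × (1 − 0.26):

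| *r* (assumed) | Spurious difference |
|---|---|
| 5% | 0.05 × 74 = 3.7 points |
| 10% | 0.10 × 74 = 7.4 points |
| 20% | 0.20 × 74 = 14.8 points |

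The planned difference is 41 − 26 = 15 points.

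**Step 5: effect on the test.** Take 306 per arm and a design effect of 1 + 49 × 0.02 = 1.98, so the effective size is 306 / 1.98 = 154.5 per arm. With true effect zero and a recorded gap *b*, the chance of a significant result favouring the intervention is Φ{[b − z√(2p̄(1−p̄)/154.5)] / √([p₀(1−p₀) + p₁(1−p₁)]/154.5)}. Here p₀ = 0.26, p₁ = 0.26 + b and p̄ is their mean.

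| Gap *b* | Share of home births misrecorded (b/0.74) | One-sided 0.05 (as stated in 4.8) | Two-sided 0.05 |
|---|---|---|---|
| 2 points | 2.7% | 11% | 6% |
| 5 points | 6.8% | 25% | 16% |
| 10 points | 13.5% | 60% | 48% |

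With no gap these would be 5% and 2.5%. This is a normal approximation that shows sensitivity; it does not predict the bias.

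**The case against.** Several stronger readings are tempting, and the documents do not support them.

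- **The public draw tells collectors the arm.** Section 4.15 says "The corresponding sequence is then used to publicly allocate each cluster to one of two groups", but those invited are health extension workers, kebele leaders and religious organisation leaders. Nothing places data collectors at the meeting or says they are told the result.
- **Table 2 makes the researcher an interviewer.** The column lists responsible persons. Sections 4.16 and 4.17 give interviewing to trained collectors under two supervisors, and 4.13 says the religious leaders deliver the sessions. The researcher appears on both sides, so the table needs clarifying, but it does not say that the researcher interviews.
- **Outcomes are in fact assessed unmasked.** That goes too far. One woman's agreement ratings raise suspicion, not certainty. Part IX comes last, so a woman's own outcomes can be recorded before it. At baseline no session or poster has yet been delivered.

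Two further objections stand. The misrecording rates are assumed, with zero in control. They also mix interviewer expectation with the woman's own wish to please, which masked interviewers would not remove; 4.15 does not claim that women are masked.

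The core survives all of this. Asking Part IX last protects that woman's answers, not those of later women in the kebele, and 4.15 offers no procedure to set against that.

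**Conclusion.** The masking sentence in 4.15 is wrong as written for the end line. Part IX asked by the same interviewers, deployment by cluster, training on the objective and allocation by kebele together make it likely that arms become known or suspected as interviewing proceeds. Posters and home interviews add to this but are not needed for the conclusion.

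The consequence is possible bias towards the intervention in participant-reported and interviewer-coded outcomes. Its size is unknown. The 3.7 to 14.8 points rest wholly on assumed misrecording of 5% to 20% in one arm and none in the other. They show only that moderate differential recording would be large relative to the 15-point target.

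**What to change.** 1. **4.15:** state that masking of outcome assessors cannot be assured at end line, and carry this into the interpretation of the self-reported outcomes. Cost: wording.
2. **4.13, Table 2:** state that the researcher, who is listed for the intervention sessions, does not conduct end-line outcome interviews. Cost: wording.
3. **ODK form:** require the outcome sections to be completed and locked before Part IX opens for each woman. This prevents back-editing but does not protect later interviews in the kebele. Cost: form programming.
4. **Field roster:** give each of the six collectors one intervention and one control kebele, which fits the 6 + 6 clusters exactly. Stable interviewer differences are then not confounded with arm. The downside is that this does not remove expectation bias and may make the arm easier to guess by contrast. Cost: a roster, no extra staff.

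Holding Part IX back until a whole kebele is finished would protect more. It is not cheap, however: women enter at any gestation below 20 weeks and are interviewed one month after delivery, so it could mean up to 682 further contacts spread over months, with long recall for early deliverers.
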